## **5.0 REQUIRED EVALUATIONS, TESTS, AND OBSERVATIONS**

The Schedule of Evaluations is shown in Appendix I.

For the duration of study participation, participants will be actively followed by review of the medical record, regular contact with the participant, and contact with pharmacy and the clinical microbiology laboratory for thrombolytic administration, new CLABSI and other catheter-related complications.

No laboratory tests will be performed for the study.

### **5.1 Pre-Study Evaluations**

At study entry, baseline data will be collected as described in Section 4.2.

### **5.2 Evaluations During Study**

Catheter resistance will be measured weekly during the study period as described in Section 4.3.

Data will be collected for catheter-related complications throughout the study period, until 21 days after the last CRM visit, as described in Section 4.5.

At weeks 4, 5, 11, and 12 (+/- 1 week) caregivers (or participants over the age of 18) will complete a questionnaire regarding acceptability of the CRM procedure. [Appendix II]

## **6.0 CRITERIA FOR REMOVAL FROM PROTOCOL AND OFF-STUDY CRITERIA**

### **6.1 Criteria for Discontinuation of Study Intervention**

- 6.1.1 Formal request of the Patient/Guardian to discontinue intervention
- 6.1.2 Formal request of the primary clinician to discontinue intervention
- 6.1.3 Permanent CVAD removal
- 6.1.4 Participant no longer attends St Jude for treatment or follow-up
- 6.1.5 Completion of 12 week intervention period

## 6.2 Off Study Criteria

- 6.2.1 Death
- 6.2.2 Permanent loss to follow-up
- 6.2.3 Formal request of the Patient/Guardian to discontinue intervention and data collection
- 6.2.4 Formal request of the primary clinician to discontinue intervention and data collection
- 6.2.5 Completion of all study requirements

## 7.0 SAFETY AND ADVERSE EVENT REPORTING REQUIREMENTS

Principal investigators are responsible for promptly reporting to the IRB any adverse events attributed to the intervention that are unanticipated, serious, and that may represent potential harm or increased risk to research participants. If an unanticipated study-intervention-related death occurs, the PI should report it to the Director of the Office of Human Subjects' Protection immediately upon becoming aware of the event by [contact], [contact], [contact], or e-mail: [[contact]](mailto:[contact])).

A reportable event entry into TRACKS will follow within 48 hours. Serious, unanticipated, study-intervention-related events must be reported within 10 working days.

In this study, adverse events related to cancer, cancer therapy and presence of a CVAD are expected. These include CLABSI, catheter occlusion and thrombosis. Adverse events directly attributable to the study intervention will be recorded according to CTCAE v4.0 and reported by the investigators.

The following definitions apply:

A **serious event** refers to any event in which the outcome is fatal or life-threatening, results in permanent disability, causes inpatient hospitalization or prolongs existing inpatient hospitalization, or is a congenital anomaly, cancer, or overdose.

An **unanticipated adverse event** refers to those not identified in their nature, severity, or frequency in the current risk documents (e.g. investigator's brochure), or consistent with the investigational plan.

The following are considered reportable: Any injuries, serious event or other unanticipated adverse events involving risk to participants or others which occur at a frequency above that considered acceptable by the investigators and the IRB. The OHSP Director or designee performs the initial review of unanticipated problems or serious adverse event reports. Internal reports of events that are unanticipated, serious, and related or possibly related to study interventions or procedures are then forwarded to the IRB Chair or designee and if necessary,

referred to the full IRB. Based on the frequency and seriousness of adverse events, the IRB Chair or Committee may deem it necessary to suspend or terminate a research study or studies.

## **8.0 DATA COLLECTION, STUDY MONITORING, AND CONFIDENTIALITY**

### **8.1 Data Collection**

The St. Jude data manager will review CRFs for accuracy and completeness. Data will then be entered into a secure database.

### **8.2 Data Collection Instructions for Affiliate Sites and Other Institutions**

Study staff will collect information from St. Jude affiliates and other healthcare institutions as necessary.

### **8.3 Study Monitoring**

Monitoring of this protocol is considered to be in the low risk category.

The Principal Investigator and study team are responsible for ensuring protocol compliance. The study team will hold quarterly team meetings and review case histories or quality summaries on participants.

Source document verification of eligibility and the informed consent process for 100% of St. Jude participants will be performed by The Eligibility Coordinators.

The Clinical Research Monitors will review up to 10% of the study participants annually for appropriateness of the informed consent process, eligibility, SAE reporting (TRACKS), and patient protocol status. Additional information may be monitored at the request of the Internal Monitoring Committee (IMC), the IRB, or other institutional administration. The Monitor will generate a formal report which is shared with the Principal Investigator (PI), study team and the IMC.

Continuing reviews by the IRB and CT-SRC will occur at least annually. In addition, SAE reports in TRACKS (Total Research and Knowledge System) will be reviewed in a timely manner by the IRB/OHSP.

### **8.4 Confidentiality**

Study numbers and medical record numbers will be used in place of participant names in study documentation. No research participant names will be recorded on the stored data collection forms. The list containing

the study number and the medical record number will be maintained in a locked file and will be destroyed after all data have been analyzed.

The medical records of study participants may be reviewed by the St. Jude IRB, FDA, clinical research monitors, etc.

## **9.0 STATISTICAL CONSIDERATIONS**

### **9.1 Analysis of Primary Objective**

To describe the feasibility of CRM in children and adolescents treated at St. Jude

The proportion of attended CRM visits which produce usable resistance data for all lumens of the CVAD will be recorded for each participant, and summary statistics, including median, range and standard deviation will be reported for the study population.

Estimated completion date: 11/01/2013

### **9.2 Analysis of Secondary Objectives**

**9.2.1** To describe patient and caregiver adherence with weekly CRM in children and adolescents treated at St. Jude

Attendance at each planned CRM visit will be recorded. Summary statistics for proportion of planned visits attended for each participant, including median, range and standard deviation will be reported for the study population.

The total number of planned weekly visits will be 12 for all participants except those who discontinue the study intervention early due to death, transfer of care or catheter removal. The number of planned visits will be capped at date of death, transfer and catheter removal respectively for these participants. For the purpose of the adherence analysis, participants who discontinue the study intervention early due to parent or clinician request will be assumed to have 12 planned visits.

**9.2.2** To explore the correlation between the results of CRM and catheter occlusion or dysfunction in children and adolescents

The relationship between CRM results and occlusion or dysfunction will be explored graphically as in Figure 5. Logistic regression models may be used to quantitate the correlation.

Occlusion events requiring treatment have been shown to occur at a rate of 2.0 - 2.2 per 1000 catheter days in pediatric oncology patients in previous

studies. [Journeycake, 2006; Dillon, 2004] Therefore, approximately 8 episodes of occlusion or dysfunction are expected during the study period.

### **9.3 Analysis for Exploratory Objectives**

#### **9.3.1 To assess acceptability of weekly CRM for participants and caregivers**

To assess acceptability over the entire study period, mean acceptability scores for each participant from all timepoints will be calculated and described. To assess change in acceptability over the study period, mean acceptability scores for all patients at each timepoint will also be calculated and described.

The test-retest reliability of the acceptability questionnaire will be assessed using the intra-class correlation for each subscale and the overall acceptability score for questionnaires completed one week apart.

Predictive validity of the acceptability questionnaire will be explored using a logistic regression model to assess whether higher acceptability scores are associated with adherence at subsequent planned visits.

#### **9.3.2 To measure the time-cost of weekly CRM**

Time taken for up to two CRM visits for each patient will be recorded and reported. Visits on week 5 and 10 for each participant will be timed. These visits have been selected as a convenience sample as they will be near the middle and end of the study. If participants do not attend these visits, the next attended visit will be timed. Time will be measured from when the line is accessed until it is flushed or de-accessed. Summary statistics such as mean, range and standard deviation of time taken will be reported.

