**Exploratory Hypotheses:**

That weekly CRM will be highly acceptable to patients and caregivers

That the mean time required for CRM will be less than 15 minutes per lumen per visit

That clinically apparent catheter-associated thrombosis and CLABSI are preceded by a measurable rise in catheter resistance which is outside the range of baseline variability

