**Planned Analyses for Exploratory Aims:**

Acceptability of the intervention will be determined by caregiver or participant

|                                                                                                                                                                                                                                                                                                                                                                                                                                                                                              |
|----------------------------------------------------------------------------------------------------------------------------------------------------------------------------------------------------------------------------------------------------------------------------------------------------------------------------------------------------------------------------------------------------------------------------------------------------------------------------------------------|
| 
responses to a custom-built acceptability questionnaire administered at 4, 5, 11 and 12 weeks.
 
Time taken for up to two CRM visits per patient will be determined at, or after, the planned 5 and 10 week visits.
 
The change in catheter resistance from baseline over time will be described for each participant. Change from baseline for measurements preceding catheter-associated thrombosis and bloodstream infections will be compared with other measurements.
 |
| 
Primary Anticipated Completion Date: 10/11/13
                                                                                                                                                                                                                                                                                                                                                                                                                                  |

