### **3.1 Inclusion Criteria**

- 3.1.1 Receiving treatment for any disease at SJRCH
- 3.1.2 Age  $\geq 5$  years to  $< 25$  years
- 3.1.3 Single or double lumen tunneled CVAD (ports will not be eligible)
- 3.1.4 Participant anticipates being present weekly at SJRCH for at least 12 weeks

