### **4.3 Measurement of Catheter-Resistance**

Catheter-resistance in each lumen of the CVAD will be measured weekly by study staff with competencies in line care. This will occur in the medicine room or inpatient floor at St. Jude.

1. The CVAD will be accessed according to usual institutional practice. This will occur immediately after collection of laboratory tests where possible to standardize the procedure. No clamp/needleless connector will be used.
2. Subjective catheter function will be assessed by flushing and aspirating the CVAD and recorded on a case report form.
3. Normal saline will be administered at a predetermined constant flow-rate by the Alaris® Syringe Module (Carefusion inc., San Diego, USA). The pressure sensor will be placed at the estimated height of the right atrium (5cm below the sternal angle).
4. Pressure will be measured using the Alaris® Syringe Module (Carefusion inc., San Diego, USA) and will be recorded on a case report form.
5. The process will be repeated twice at 4 different flow-rates (usually 10ml/h, 50ml/h, 100ml/h, 150ml/h) for each lumen. Only flow-rates within the normal range for the population will be used. Figure 6 shows expected results for this procedure.
6. The line will be flushed and locked according to usual institutional practice.

If total occlusion of one or both lumens is identified at step 2, CRM will not be performed on involved lumens until patency is achieved.

It is anticipated that the CRM procedure will take 10-20 minutes per lumen to complete.

At each weekly visit, participants will be offered a \$5 gift card or other item of similar value.

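### The time-cost hypothesis is stated per lumen, but section 9.3.2 times and averages whole visits, so the planned mean does not address it

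*Protocol*

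**What the plan says.** The Exploratory Hypotheses in the study summary give the threshold and its unit: "That the mean time required for CRM will be less than 15 minutes per lumen per visit". Section 4.3 gives the expected duration in the same unit, "It is anticipated that the CRM procedure will take 10-20 minutes per lumen to complete", and requires the measurement to be carried out separately on each lumen: "The process will be repeated twice at 4 different flow-rates (usually 10ml/h, 50ml/h, 100ml/h, 150ml/h) for each lumen".

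The analysis text uses another unit. Section 9.3.2 states: "Time taken for up to two CRM visits for each patient will be recorded and reported". It defines the interval ("Time will be measured from when the line is accessed until it is flushed or de-accessed") and the summary ("Summary statistics such as mean, range and standard deviation of time taken will be reported"). The Planned Analyses for Exploratory Aims in the study summary also name the visit as what is timed: "Time taken for up to two CRM visits per patient will be determined at, or after, the planned 5 and 10 week visits".

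Section 3.1 admits both single- and double-lumen tunneled devices. Nowhere does the protocol time lumens separately, divide visit time by lumens, or split the time summary by lumen number.

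**The concern.** The hypothesis and its planned measure are in different units. With one lumen the two coincide. With two, the visit contains two runs of the procedure, so its duration is up to twice the per-lumen time. A mean taken over all timed visits mixes the two kinds, and its value depends on how many double-lumen catheters happen to be enrolled.

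Two things are at stake. A reader who sets the reported mean beside the only threshold in the protocol would be comparing minutes per visit with minutes per lumen. And the reported mean would not carry over to a population with a different share of double-lumen devices. Because 15 minutes is the midpoint of the protocol's expected 10-20 minutes per lumen, the difference in unit is large enough to change which side of the threshold the result falls on.

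**Working it through.** There is no derived figure in the protocol to reproduce: 15 minutes is a chosen threshold, and this aim has no sample-size or power calculation. The check is arithmetic on the stated durations.

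**Inputs**
- Threshold: 15 minutes per lumen per visit (Exploratory Hypotheses).
- Expected duration: 10-20 minutes per lumen (section 4.3).
- Lumens per device: 1 or 2 (section 3.1).
- Share of visits that are double-lumen, *d*: not given, so taken as an assumption over 0-100%.
- Lumens measured one after the other with no shared time: an assumption, relaxed in step 4.

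**Step 1. One double-lumen visit.** Visit time = 2 × *t*, where *t* is minutes per lumen. For *t* = 10 to 20, this gives 2 × 10 = 20 to 2 × 20 = 40 minutes. Even at the protocol's lower bound, the visit exceeds 15 minutes while the per-lumen time is under 15.

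**Step 2. Range over which the two units disagree.** The visit time reaches 15 when 2*t* = 15, so *t* = 7.5. The hypothesis is met while *t* < 15. For 7.5 ≤ *t* < 15, a double-lumen visit lasts from 15 to just under 30 minutes although the hypothesis holds.

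**Step 3. Mean over a mixed sample.** Mean visit time = *t* × (1 + *d*). It reaches 15 at *d* = 15/*t* − 1.

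| Minutes per lumen | Visit mean, *d* = 0 | *d* = 50% | *d* = 100% | *d* at which visit mean = 15 |
|---|---|---|---|---|
| 10 | 10 | 15 | 20 | 50% |
| 12 | 12 | 18 | 24 | 25% |
| 14 | 14 | 21 | 28 | 7% |

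The same per-lumen time of 12 minutes thus yields a reported mean anywhere from 12 to 24 minutes, according to the lumen mix alone.

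**Step 4. Shared time.** Suppose each visit has a fixed *o* minutes for access and set-up, plus *m* minutes per lumen. A single-lumen visit takes *o* + *m* and a double-lumen visit *o* + 2*m*. The values of *o* and *m* are assumed.

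| *o* | *m* | Single visit | Double visit | Double visit ÷ 2 |
|---|---|---|---|---|
| 2 | 5 | 7 | 12 | 6.0 |
| 5 | 5 | 10 | 15 | 7.5 |
| 2 | 8 | 10 | 18 | 9.0 |
| 5 | 8 | 13 | 21 | 10.5 |
| 2 | 10 | 12 | 22 | 11.0 |
| 5 | 10 | 15 | 25 | 12.5 |

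The disagreement remains in every row except the first, where the procedure is short enough to be under 15 minutes either way. The table also shows the limit of dividing by lumens: at *o* = 5 and *m* = 8, the figure is 13 for a single-lumen visit and 10.5 for a double, so some dependence on lumen mix stays.

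**Step 5. Direction.** Visit time divided by one or two lumens is never longer than the visit itself. A whole-visit mean below 15 minutes would therefore still imply that the hypothesis is met. Only a visit mean of 15 or more is uninformative, and that is the likely case at 10-20 minutes per lumen unless most visits are single-lumen and quick.

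**The case against.** The strongest reply is that nothing is lost. Visit time is recorded, catheter type is collected at enrollment (section 4.2), and pressures are recorded as the procedure is repeated for each lumen (section 4.3). The number of lumens measured at a timed visit should therefore be recoverable, and the per-lumen mean needs one division. This stands. A reader might infer that the data cannot be compared with 15 minutes at all; the protocol does not support that. It is the planned summary, not the data collected, that is in the wrong unit.

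Second, section 9.3.2 plans no test or formal comparison with 15 minutes, and its list of summary statistics is open-ended. A reader might infer that the hypothesis will be declared to have failed on the visit mean. The protocol does not say so, and the threshold appears only with its per-lumen unit attached. This too stands, and it limits the point to interpretation.

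Third, total visit time is a sensible measure in itself. Objective 1.3.2 is simply to measure time-cost, and for families and staff the burden is the whole visit. That is a reason to keep visit time, reported alongside the per-lumen figure.

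Fourth, *the line* in the clock definition might be read as a single lumen. But both places that describe the timing name a visit as the unit, and the protocol says lumen elsewhere when it means lumen.

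A reader might also suspect that the clock takes in routine blood collection. Section 4.3 places the access for CRM directly after laboratory collection where possible, so the text gives little ground for changing the start of the clock.

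Lumen-level derivations could be left to an analysis plan that is not shown. Here, though, the protocol is not silent: it fixes a clock and a summary that differ in unit from its own hypothesis.

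**Conclusion.** The mismatch holds. The whole-visit mean planned in section 9.3.2 depends on the lumen mix and does not address the hypothesis as stated. Without shared set-up time, a double-lumen visit at the expected 10-20 minutes per lumen takes 20-40 minutes, and the visit mean passes 15 minutes once the double-lumen share exceeds 50%, 25% or 7% at 10, 12 or 14 minutes per lumen. The double-lumen share and any shared set-up time are not in the protocol; moderate overhead of 2-5 minutes narrows the gap without closing it when measurement takes 8-10 minutes per lumen.

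The consequence is minor. It concerns one exploratory, descriptive aim and leaves the primary outcome, sample size and error rates untouched. The documents give no basis for requiring a confidence interval against 15 minutes or a different start to the clock.

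**What to change.** In section 9.3.2, and in the matching lines of the study summary:

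1. Record the number of lumens actually measured at each timed visit. Use this rather than the catheter type, because section 4.3 omits a totally occluded lumen until patency is achieved.
2. Report visit time divided by lumens measured, and name this as the quantity set against 15 minutes.
3. Report total visit time as well, separately for single- and double-lumen visits.

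Suggested wording: *For each timed visit, the time taken will be divided by the number of lumens measured, and the mean, range and standard deviation of this per-lumen time will be reported in relation to the 15-minute hypothesis. Total visit time will be summarised separately for visits with one and with two lumens measured.*

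The cost is one CRF field at no more than two visits per participant. The drawback is that access time shared between lumens makes the divided figure only an approximation to true per-lumen time; reporting the two kinds of visit separately lets the reader see how much this matters.

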#### **9.3.3 To explore the correlation between results of CRM and catheter-associated thrombosis or CLABSI in children and adolescents**

The relationship between CRM results and thrombosis or CLABSI will be explored graphically as in Figure 5 and in 9.2.2. Logistic regression models may be used to quantitate the correlation.

## **10.0 OBTAINING INFORMED CONSENT**

Eligible patients will first be approached by the patient's primary physician or a member of the study team regarding the study purpose, methods and design details.

Both verbal and written assent and consent procedures will be completed in a private room and following St. Jude Children's Research Hospital institutional

guidelines. Verbal assent will be obtained from participants 7 to less than 14 years old and written assent from participants 14 to less than 18 years old. The consent/assent process will be documented in the medical record per institutional guidelines.

Research participants and parents may decline participation without any negative repercussions. Declinations will be documented in the research records and examined for any possible patterns.

If the informed consent process occurs on a different day to study entry, a discussion to assure continued interest in participation will occur at the time of screening and will be documented in the study database.

All patients who meet eligibility criteria regardless of gender or minority status are fully eligible to participate in this study. All data will be kept confidential and stored in locked offices.

